**Objective:**

The app aims to increase the use of campus resources that address student mental health and wellness by improving the awareness of these resources through user-designated preferences that are established on the initial use of the app and then iteratively refined as it is used. The app is linked to the campus student’s electronic health record so that health and wellness services can be coordinated and enhanced and the student journey to and through care become more seamless. The long-term objective is to leverage data from both the app and electronic health record to improve individual and population health for the entire campus.

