**Figure 2 figure2:**
[figure not shown]
Logic model. ACTRI: Altman Clinical and Translational Research Institute; CAPS: Counseling and Psychological Services; H&W: Health and Wellness; R&D: Research and Development; UC: University of California; UCSD: University of California San Diego.

The immediate, tangible output of the project activities will include a fully functional mobile app for student mental health and wellness support, an increased awareness and utilization of campus mental health and well-being resources, and outreach and education for campus service providers to familiarize them with the app. The committee made recommendations about the following short-term, intermediate, and long-term changes to be assessed as a result of the project and how these lead to broader systemic change.

The short-term outcomes include improved mental health and wellness literacy and help-seeking attitudes among students, increased engagement with evidence-based self-management strategies, and enhanced feelings of social connectedness and reduced isolation.Intermediate outcomes include reduced symptoms of anxiety, depression, and other common mental health issues and increased utilization of the app and on-campus counseling and support services.Long-term outcomes are expected to be a positive shift in the campus culture around mental health and well-being; sustainable adoption and integration of the app through students; and improved overall student health, satisfaction, and success outcomes.The broader systemic changes that the project aims to contribute to over time would be a healthier and more resilient university student population, leading to reduced mental health–related costs and productivity losses for universities.

The committee emphasized the importance of viewing this logic model as a dynamic framework, subject to refinement and adaptation, as new evidence emerges and the project evolves. They also stressed the need for rigorous evaluation at each stage to ensure that the project is meeting its intended goals and to inform continuous improvement efforts.

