### Evaluation Plan

Using the logic model as a foundation, the advisory committee and development team identified key areas that required evaluation. They prioritized metrics that would provide actionable insights for improving the app and its integration into existing campus mental health and wellness services. Drawing on their collective expertise, the committee discussed various data collection methods. They aimed for a mixed methods approach to capture both quantitative and qualitative data, ensuring a comprehensive evaluation. Moreover, recognizing the evolving nature of digital health interventions, the committee built in mechanisms for ongoing review and refinement of both the app and the evaluation process itself.

Throughout this process, the committee emphasized the importance of flexibility and adaptability, acknowledging that the evaluation plan may need to be adjusted as the project progresses and new insights emerge. They also stressed the need for ongoing communication and collaboration among all stakeholders involved in the implementation and evaluation of the student mental health and wellness app. The evaluation questions that could address important outcomes are listed below.

To what extent does the use of the mobile app lead to reductions in symptoms of anxiety, depression, and other common mental health issues among students?How many students download and actively use the app on a regular basis? What user characteristics or engagement patterns are associated with better outcomes?How well is the app integrated with campus counseling, health, and other support services? What are the facilitators and barriers to this integration?What are the key lessons learned from implementing the app, and what modifications or additional support are needed to sustain and scale the program in the long term?

Data collection methods will include pre-post surveys of app users to assess changes in knowledge regarding campus resources, presence and severity of mental health symptoms, emotional self-awareness, stigma and other barriers to care, confidence in and degree of help-seeking behaviors, and overall app usage data (downloads, login frequency, feature engagement). We also plan to conduct interviews and focus groups with app users, campus mental health staff, and other relevant stakeholders.

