For continuous quality improvement, we plan to regularly review the evaluation results with the project team to identify the areas for app refinement and programmatic enhancements and use data to secure continued funding and support for sustaining and scaling the app-based program.

This evaluation plan (Table 1) outlines a mixed methods approach to assess the student mental health and wellness app project on multiple levels—individual student outcomes, community reach and usage, operational feasibility, and long-term sustainability. The plan emphasizes the importance of utilizing evaluation findings to drive ongoing improvement and broader dissemination of effective practices. Rigorous data collection, analysis, and reporting will be critical to demonstrating the value of this initiative to university stakeholders and external partners.

The evaluation team designed a process to evaluate cohorts of the students biannually. This process enables the team to monitor trends and changes at the population level across campus and assess the outreach, effectiveness, and impact of the app. In the first cohort, students who are new to the campus (ie, freshman, transfer, and first-year medical students) will be invited to enroll in the assessments. They will be required to provide informed consent before participating and will be compensated for their time and engagement in the quantitative and qualitative assessments (Multimedia Appendix 3).

**Table 1 table1:** A summary of the evaluation plan for the mental health and wellness app (Willow).

Evaluation domains	Outcomes	Key performance indicators	Data sources and collection method
Campus services awareness, accessibility, and utilization	Improving access to mental health resources, improved efficiency of use of resources for individual psychological counseling, referral to the app by counseling and psychological services & health and wellness providers, improved utilization of on-campus services	Satisfaction, in-app services usage, Counseling and Psychological Services usage, effectiveness and relevance of the app, utilization of campus services	App analytics, in-app rating systems, in-app surveys and questionnaires, focus groups; interviews with counseling and psychological services & health and wellness providers

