### Data Analysis and Interpretation

#### Quantitative Analyses

Quantitative data will be analyzed using appropriate statistical software (SPSS or similar) to determine if users are gaining knowledge about the featured services and resources and if the services and resources that are being highlighted are matching with the desires of the target populations.

To assess changes in mental health and wellness outcomes within and between cohorts over time, we will conduct repeated measures analysis of variance and mixed-effects modeling. These approaches are well-suited for analyzing longitudinal data with repeated observations per participant. The primary dependent variables will include standardized scores from validated instruments measuring mental health and well-being. Independent variables will include cohort membership, time (semester), usage of the Willo app, and engagement with university support services. Interaction terms (eg, time × app usage) will be included to assess potential moderating effects.

A power analysis was conducted using a conservative estimate of small-to-moderate effect sizes, consistent with those commonly reported in similar longitudinal mental health studies. With 850 participants per cohort and repeated measurements across 8 time points, the study is adequately powered (≥80%) to detect meaningful changes in outcomes over time and between groups, assuming an α level of .05.

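### Service engagement, an intended result of the app, is listed as an independent variable beside app usage, so an adjusted app coefficient would not give the app's overall effect on mental health

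*Protocol article*

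**What the plan says.** The protocol article's Quantitative Analyses section sets the outcomes of the longitudinal models: "The primary dependent variables will include standardized scores from validated instruments measuring mental health and well-being". It then gives the predictors: "Independent variables will include cohort membership, time (semester), usage of the Willo app, and engagement with university support services". Interaction terms are added, with time by app usage as the only example. The methods named are repeated measures analysis of variance and mixed-effects modelling.

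Elsewhere the article gives service use a different role:

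- The abstract's Objective: "The app aims to increase the use of campus resources that address student mental health and wellness by improving the awareness of these resources".
- The Logic Model section lists among the intermediate outcomes "increased utilization of the app and on-campus counseling and support services", next to reduced symptoms.
- Table 1, first domain, lists "improved utilization of on-campus services" as an outcome. It also lists referral to the app by counselling and health and wellness providers.

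The first question in the Evaluation Plan is: "To what extent does the use of the mobile app lead to reductions in symptoms of anxiety, depression, and other common mental health issues among" students. It is not limited to an effect that bypasses campus services.

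**The concern.** By the article's own account, one chain of benefit runs from app use to greater use of services to better mental health. A variable in the middle of that chain is a mediator. If it sits in the model beside app usage, the app coefficient compares students with different app use but the same service engagement, and so leaves out the benefit that arises because the app led students to services.

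There is a second problem. Students in greater need are likely to use services more and to score worse. Holding service engagement fixed then links app use to need, even if the two were unrelated before, and this bias has no fixed sign.

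At stake is the answer to the first evaluation question. The Evaluation Plan also says that results will support the case for continued funding. The time by app usage term does not help, because it would be estimated with service engagement in the same model.

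**Working it through.** **Plan's own figure.** The only figure in this section is power of at least 80% with 850 participants per cohort, 8 time points and α = .05. It cannot be reproduced, because no numerical effect size, within-person correlation, test or app-use split is given. For scale, the smallest difference detectable with 80% power (two-sided α assumed, SD 1, one time point) is (1.960 + 0.842) × √(2/n):

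- 850 v 850: 2.802 × √(2/850) = 0.136 SD.
- 425 v 425 (an assumed even split by app use within one cohort): 2.802 × √(2/425) = 0.192 SD.

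The point does not depend on the power claim.

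**Check 1: what adjustment removes.** All inputs are assumptions, because the article gives none. Higher scores are better.

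- Overall app effect T = 0.20 SD.
- Share of it running through services: s.
- Effect of app use on service engagement: a = 0.5.
- Effect of service engagement on the score: b = T·s/a.
- Direct effect: c = T(1 − s).

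Without services in the model, the app coefficient is c + a·b = T = 0.20 at every s. With services in the model it is c = T(1 − s).

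**Check 2: a shared cause.** Let need raise service engagement and lower the score, each with path strength u = 0.4, and let the variance of services given app use be 1. The service coefficient is then biased by −u² = −0.16. The app coefficient shifts by +a·u² = 0.5 × 0.16 = +0.08, giving T(1 − s) + 0.08. The model without services still gives 0.20, because app use is taken as unconfounded here.

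| Share through services | Without services | Adjusted, no shared cause | Adjusted, shared cause |
|---|---|---|---|
| 0% | 0.20 | 0.20 | 0.28 |
| 25% | 0.20 | 0.15 | 0.23 |
| 50% | 0.20 | 0.10 | 0.18 |
| 75% | 0.20 | 0.05 | 0.13 |
| 100% | 0.20 | 0.00 | 0.08 |

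A least-squares simulation with 2,000,000 records agreed with every cell to within 0.003.

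In the last column the two errors cancel where 0.20·s = 0.08, at s = 40%. Below that share the adjusted coefficient overstates the overall effect, and above it the coefficient understates it.

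Approximate power for 425 v 425, with no shared cause, falls from 83% at 0.20 SD to 59% at 0.15, 31% at 0.10 and 11% at 0.05.

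**Check 3: the reverse arrow.** Table 1 expects providers to refer students to the app, so service contact can also precede and cause app use. Assume standardised variables and a symptom score where lower is better:

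- services to app: 0.3
- services to symptoms: −0.2
- need to services and need to symptoms: 0.3 each
- true app effect: −0.08

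Leaving prior services out gives −0.08 + 0.3 × (−0.2) + 0.3 × 0.3 × 0.3 = −0.08 − 0.06 + 0.027 = −0.113. Adjusting for prior services returns −0.08, because in this set-up need reaches app use only through services. Engagement before app use therefore belongs in the model. Engagement after it does not, if the overall effect is wanted.

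**The case against.** **The loss is not total.** A reader might infer that the planned model removes the app effect altogether and would show little or nothing even if the app works. The documents do not support that. The logic model names routes that need not pass through campus services: "increased engagement with evidence-based self-management strategies, and enhanced feelings of social connectedness and reduced isolation". Only the mediated share is lost, and the article gives no figure for it. With a shared cause the adjusted coefficient can even exceed the overall effect. This objection stands and limits the claim.

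**The text does not fix one model.** The sentence lists what the independent variables will include, across two methods. It does not say that all four enter together, or that this coefficient alone answers the first evaluation question. Service engagement may also be of interest as a predictor in itself. This stands in part. A single list followed by interaction terms is most naturally read as one model, and the article describes no model without service engagement, no mediation analysis and no direct-effect target.

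**Service contact may be a confounder.** Provider referral makes this credible, and Check 3 shows that omitting prior contact can bias the result. This stands, and it rules out simply deleting the variable.

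**Service use is already an outcome.** Table 1 lists it and Table 2 includes a survey of resource usage. True, but the longitudinal models name only mental health and well-being scores as primary dependent variables. Listing service use as an outcome in Table 1 does not change its role as a predictor there.

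**Conclusion.** The concern holds in this limited form. The article names service engagement as a predictor beside app usage while presenting higher service use as an intended result of the app. A model that follows the list, with engagement measured during or after the app exposure, does not estimate the overall effect that the first evaluation question asks about.

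It loses the mediated share and may add bias of either sign. Under the assumed 0.20 SD effect the adjusted coefficient runs from 0.00 to 0.20 SD without a shared cause and from 0.08 to 0.28 SD with one. These figures show the mechanism only; neither the size nor the direction of the net bias can be derived from the article.

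The conclusion assumes that the listed variables enter one model and that the engagement variable is not confined to the period before app use. The article states neither point outright. Leaving out later engagement does not make self-chosen app use unconfounded, so the result remains an association.

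**What to change.** State in the analysis section, before any data are analysed (the Results section reports none as of March 2025):

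1. The main model for app usage and mental health scores excludes service engagement that is concurrent with or later than the app exposure.
2. Only engagement that precedes the exposure, at baseline or at an earlier wave, is kept as a covariate. App usage must then be defined for the interval after that measurement. Because consent is given inside the app, the baseline question should refer to the period before the app was used.
3. Later service use is modelled as an outcome in its own right, in line with Table 1.
4. Any model adjusted for later engagement, or a mediation analysis, is reported as a labelled secondary analysis, with the caveat that need may drive both service use and symptoms.

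The cost is one or two extra models on data already planned, and the work of putting service use and app use in time order.

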#### Qualitative Analyses

We will employ Rapid Qualitative Analysis drawing on the structured and pragmatic methodology [30,31], which is particularly well-suited to applied health and implementation research settings where timely yet rigorous analysis is needed. Rapid Qualitative Analysis involves structured data reduction by using summary templates and matrix-based analysis to support both cross-case comparison and theme identification while maintaining methodological transparency and feasibility. To enhance trustworthiness, we will implement the following strategies.

Credibility: analyst triangulation and regular team-based discussions will be used to verify interpretations.Dependability: a documented audit trail will capture analytic decisions and changes throughout the study.Confirmability: independent checks of data summaries will ensure interpretive consistency.Transferability: contextual information will be included to support the applicability of findings beyond the sample.

We will incorporate reflexivity throughout the analytic process, as recommended in reflexive approaches to qualitative research. Analysts will document positionality, and the team will engage in critical discussions about how their perspectives shape interpretation. In doing so, we also align with the call for “knowing practice” [32] in thematic analysis—owning our theoretical stance, making reflexive choices explicit, and avoiding the uncritical mixing of incompatible analytic paradigms.

## Results

As of March 2025, we are in the process of data collection. Preliminary data that have been collected include >600 responses to surveys from freshman, undergraduate transfer, and medical students. A second round of survey assessments to measure change is expected in April to May 2025. We have also conducted 2 focus groups with undergraduate freshman to date. Two focus groups with undergraduate transfer students and one with medical students are planned for April-May 2025. No data analyses have been performed as of yet. These data will be the baseline for the metrics used, and we plan to repeat the data collection with every cohort biannually.

## Discussion

The rising prevalence of mental health challenges among college students underscores the critical importance of addressing student mental health and wellness in higher education settings [33]. This project’s multifaceted approach, combining digital technology, user-centered design, and evidence-based interventions, represents a promising step toward improving access to mental health resources and support for university students.

By leveraging mobile app technology and potentially incorporating artificial intelligence–driven features, this initiative aligns with the increasingly tech-savvy nature of today’s student population. Knowing the rapid evolution of digital technologies, we tried to emphasize iterative modeling and personalized interventions in this app to effectively address student’s wellness challenges [27]. As digital natives, current and incoming university students are likely to find app-based mental health support more approachable and accessible than traditional services alone. This technological approach not only meets students where they are but also has the potential to reduce the stigma associated with seeking help—a significant barrier to mental health care utilization among young adults [34].

A key rationale for the potential effectiveness of this app lies in its ability to address one of the most critical barriers to student mental health support: timely access to resources and information. By providing a readily accessible platform that offers immediate information about available resources and services, the app has the potential to bridge the gap between students’ needs and appropriate support systems. This proactive approach is supported by research indicating that timely access to mental health resources is associated with better academic performance, higher retention rates, and improved mental health outcomes and overall well-being among university students [35,36].

The user-centered design process employed in this project is a key strength, ensuring that the final product is tailored to the specific needs and preferences of university students. By involving students at every stage, from the initial gap analysis to feature selection and usability testing, the app is more likely to resonate with its intended users and achieve higher engagement rates. This approach aligns with best practices in digital health intervention development and increases the likelihood of the app’s effectiveness and sustained use [37,38].

The integration of the mental health app with the campus student electronic medical record represents a significant advancement in coordinated care for college students. This linkage allows for a more comprehensive and holistic approach to student health and wellness, enabling seamless coordination between digital interventions and traditional health care services. The long-term objective of leveraging data from both the app and electronic medical record to improve individual and population health for the entire campus is particularly promising. This data integration could enable sophisticated predictive analytics and population health management strategies, allowing for the early identification of at-risk students and the development of targeted preventive interventions [39].

The potential for scalability to other college campuses is another significant aspect of this project. By designing the app with scalability in mind, there is an opportunity to extend its reach and impact across different student populations, potentially benefiting hundreds of thousands of students. This scalability also offers the possibility of gathering large-scale data on student mental health trends and intervention effectiveness, which could inform future research and policy decisions [40].

The interdisciplinary nature of the project, bringing together expertise from software engineering, public health, mental health and wellness, and design, is a testament to the complex, multifaceted nature of student mental health and well-being challenges. This collaborative approach ensures that the app is not only technologically sound but also grounded in public health principles and current best practices in mental health and wellness care. The data generated from this project could serve as a rich resource for researchers across these disciplines, potentially spurring new collaborations and lines of inquiry. For example, public health researchers might collaborate with artificial intelligence specialists to develop predictive models for mental health trends on university campuses.

It should be noted that, as with any digital health intervention, issues of data privacy, security, and ethical use of artificial intelligence (if implemented) must be carefully considered and addressed [41]. Ongoing evaluation and refinement of the app based on user feedback and outcome data will be crucial to ensuring its long-term effectiveness and relevance.

In conclusion, this project represents an innovative, student-centered approach to addressing the pressing issue of college student mental health. By combining technological innovation with evidence-based practices and interdisciplinary collaboration, it has the potential to significantly improve access to mental health support for university students. As the project moves forward, continued emphasis on user engagement, privacy protection, and integration with existing campus services will be key to its success and potential for broader impact across the University of California system and other institutions of higher education [42].

We plan to disseminate the findings and lessons learned from this project through peer-reviewed publications and multimedia channels, including social media, news, university websites, and conference presentations.

